Currently, the Department of Obstetrics and Gynecology at our institution has decided to launch the ERAS protocol for patients scheduled to undergo elective laparoscopic gynecologic surgery. This study is a follow-up study on the anxiety-reducing effect of chewing gum during the fasting period before surgery. Patients participating in the ERAS protocol were set as a control group and sham feeding using gum was performed during the fasting period in the experimental group. The purpose of this study is to find out if chewing gum plus carbohydrate is effective in reducing anxiety and discomfort before surgery.

3) design: Single-center, randomized controlled study, investigator blinded.

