**6. Study participants**

1) Inclusion criteria

(1) ASA class I-III adult patient (age 18 and under 70)

(2) Patients undergoing the laparoscopic gynecological surgery

2) Exclusion Criteria

(1) Pediatric (under 18)

(2) Old age (over 70)

(3) Pregnant and nursing mothers

(4) Patients with unstable vital signs (emergent conditions)

(5) Patients who are at high risk of aspiration: persons with a BMI of 30 or more, gastroesophageal reflux, achalasia, enteropathy, diabetes mellitus, and with a history of gastrointestinal tumor

(6) current medication affecting gastrointestinal motility

(7) uncontrolled liver or kidney disease

(8) Emergency surgery

(9) Patients who do not agree to participate in the study

3) Protection measures when recruiting vulnerable participants

All study subjects will obtain informed consent 1 day in advance and will spend at least 30 minutes sufficient time for explanations. In the case of subjects with reduced understanding and judgment, additional protective measures such as obtaining additional consent from the guardian (or representative) will be taken.

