The patient is assigned to either the experimental group or control group on a random basis on the eve of the operation. There is no intervention other than chewing gum during fast times between the two groups of patients, and subsequent anesthesia and pre-anesthesia examinations will be conducted according to a standardized protocol. The randomization list was generated by a random permuted block design with a block size of two. The allocation information is sealed in an opaque envelope and piled up in a cabinet. Gynecologist open the sealed envelope, in turn, to confirm the assignment information and distributed or not distributed chewing gum, accordingly. Randomization information is managed so that the list is not disclosed to the evaluator and only primary investigators can know. After entering the operating room, both the control group and the test group proceed according to the same study protocol, and both gastric volume measurements and acidity records are recorded by the [name]. Anxiety levels prior to surgery and uncomfortable symptoms related to fasting will be recorded by an anesthesiologist who is not participating in the study based on patient self-report. Postoperative gastrointestinal motility recovery and postoperative recovery questionnaires were completed by the patient under the guidance of an independent maternity ward nurse and attending physician.

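### A fixed block size of two, with envelopes opened in turn, lets anyone who knows the block size and the previous assignment predict half of the allocations with certainty

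*Protocol*

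**What the plan says.** Section 9 of the protocol, under Randomization and blinding, fixes the method: "The randomization list was generated by a random permuted block design with a block size of two". It names no stratification factor and no variation in block size, and section 4 describes a single-center trial, so the text points to one list.

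Concealment rests on envelopes: "The allocation information is sealed in an opaque envelope and piled up in a cabinet". The same paragraph says who uses them and how: "Gynecologist open the sealed envelope, in turn, to confirm the assignment information and distributed or not distributed chewing gum, accordingly". It does not say whether the envelopes are numbered or how many gynecologists open them. On access to the list it says: "Randomization information is managed so that the list is not disclosed to the evaluator and only primary investigators can know".

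On timing, section 9 states: "The patient is assigned to either the experimental group or control group on a random basis on the eve of the operation". Section 6 states: "All study subjects will obtain informed consent 1 day in advance". Section 11 also places the review of patient information on the day before anesthesia. Section 7 sets the size at 104 patients, 52 per group. Section 13 names the APAIS score and anxiety-related symptoms as primary outcomes, and section 9 has anxiety and fasting symptoms recorded from patient self-report.

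**The concern.** Allocation concealment requires that nobody who can affect enrolment knows the next arm before the patient is committed to the trial. A 1:1 block of two has only two forms, gum then control or control then gum. Once the first envelope of a pair has been opened, the second is settled. The envelope may be perfectly opaque and still hide nothing, because the information lies in the previous assignment.

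The protocol gives that information to the person who opens the envelopes in turn and acts on them. Gum is also visible on the ward, so others may learn it. The block size is printed in the protocol, and strict pairing is easy to notice in practice.

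At stake is the comparability of the arms. If someone who can predict the next arm can also approach, defer or reorder patients, the arms may differ at baseline on something related to anxiety. An analysis cannot reliably detect or remove that afterwards.

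**Working it through.** **Inputs.** Block size 2 and opening in sequence (section 9); N = 104 at 1:1 (section 7). The protocol gives no figure for predictability. Its total follows from 47 × 1.10 = 51.7, rounded up to 52 per arm, and 2 × 52 = 104. Only this total is used below.

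**Block of two.** 104 / 2 = 52 blocks. The first allocation of each block is an even guess and the second is certain.

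- Certain allocations: 52 of 104 = 50%.
- Correct best guesses: 52 × 0.5 + 52 × 1 = 78 of 104 = 75%.

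**Other fixed sizes.** For a block of 2m patients, m per arm, and an observer who knows the size and sees past assignments:

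- Share certain = 1 / (m + 1).
- Correct guesses per block, always guessing the arm with more places left = m + ½ × [2^(2m) / C(2m, m) − 1].

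For m = 1 these give 1/2 and 1 + ½ × (4/2 − 1) = 1.5 of 2 = 75%, as above. For m = 2 they give 1/3 and 2 + ½ × (16/6 − 1) = 2.83 of 4 = 70.8%. Full enumeration of the blocks gives the same values.

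**Randomly mixed sizes.** These come from 1,500 simulated lists of 104 per mix. The observer knows which sizes are possible but not their order, and updates by Bayes' rule after each assignment.

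| Block sizes | Certain | Out of 104 | Best-guess accuracy |
|---|---|---|---|
| fixed 2 (protocol) | 50.0% | 52 | 75.0% |
| fixed 4 | 33.3% | about 35 | 70.8% |
| fixed 6 | 25.0% | 26 | 68.3% |
| fixed 8 | 20.0% | about 21 | 66.6% |
| mixed 2/4 | about 11.0% | about 11 | about 72% |
| mixed 4/6 | about 5.5% | about 6 | about 69% |
| mixed 4/6/8 | about 2.3% | about 2 | about 68% |

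Mixing sizes mainly removes certainty. It barely changes how often a guess is right, and fixed blocks of 6 or 8 do as well on that measure.

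**Cost of imbalance.** If a 4/6/8 list stops mid-block, the arms differ by at most 4 patients (half of the largest block). For 54 against 50, the variance factor is 1/54 + 1/50 = 0.03852, against 2/52 = 0.03846 when balanced, an increase of about 0.15%.

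**Opportunity to act on a prediction.** Consent is taken one day ahead, patient information is reviewed the day before anesthesia, and assignment is made on the eve of surgery. All three fall in the same window. Nothing requires consent and eligibility to be recorded, or the order of patients fixed, before the next arm can be predicted.

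**The case against.** The strongest reply is that predictable is not the same as known, and known is not the same as biased. To predict, a person must know or infer the block size, know the previous assignment and know the position within the pair. If several gynecologists open envelopes, each would need to learn what the last one found. This stands, and the conclusion is conditional for that reason.

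Nor does the protocol say that the gynecologist who opens the envelope screens patients, obtains consent or sets the order. A reader might infer that selection bias is built into the treatment effect. The documents do not support that: they leave the route open without showing that anyone can take it, and the direction of any bias is unknown.

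A reader might also put a size on the bias in VAS points, because section 7 sizes the trial on VAS. Any such number would only restate an assumed shift between patients, on a scale that section 13 does not name as primary. None is given here.

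Two further inferences go too far. One is that an evaluator who learns one patient's arm also learns the partner's. That holds only if the evaluator knows who is paired with whom, and the list is withheld from the evaluator. The other is that "Single-center, randomized controlled study, investigator blinded" contradicts the primary investigators' access to the list. The phrase can reasonably mean blinded assessors, which matches the blinded intubation rater and the evaluator without the list. Access to the list still bears on concealment, but it does not prove a contradiction.

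**Conclusion.** The concern holds as a weakness of allocation concealment that the protocol itself fixes. Under a published block size of two, 52 of 104 allocations (50%) follow with certainty from the one before, and 75% can be guessed correctly. Nothing elsewhere in the protocol repairs this.

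The figures assume one unstratified 1:1 list used in order, and an observer who knows the block size and sees each assignment. Harm to the comparison needs one more condition: that this observer influences who enters, when, or in what order. That is a risk the protocol leaves open, not a demonstrated bias. It deserves correction because subjective primary outcomes leave little protection if it occurs, and because prevention is cheap.

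**What to change.** 1. Generate the list with randomly varying block sizes such as 4, 6 and 8, leaving out size 2. If enrolment has begun, do this for the remaining allocations. Keep the sizes out of the documents given to enrolling and assessing staff.
2. Require consent and eligibility to be recorded, and the patient's number written on the envelope, before it is opened. This does not stop prediction of the next arm. It commits the patient before the arm is revealed and makes later swapping visible.
3. Restrict access to the list to someone not involved in enrolment or assessment, in place of the present wording that "the list is not disclosed to the evaluator and only primary investigators can know".

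Certain allocations fall from 50% to about 2% (about 5.5% with a 4/6 mix). Best-guess accuracy falls only from 75% to about 68%, so the block change alone is not full protection and step 2 matters as well.

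The cost is a new list and refilled envelopes, a minor protocol amendment (the text says the list already exists), and a possible imbalance of a few patients with negligible effect on precision. No extra patients or visits are needed.

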- **standardized anesthesia protocol**

Standard ASA monitoring including noninvasive blood pressure, EKG, pulse oximetry, and bispectral index (BIS) monitoring will be applied. After denitrogenation with 80 % oxygen, general anesthesia will be induced with propofol and remifentanil using target-controlled infusion (Orchestra® Base Primea; Fresenius Kabi, Brezins, France), and intravenous rocuronium 0.8 mgkg^-1^. Another investigator who is not aware of group allocation will perform intubations and evaluate the degree of oral secretion during intubation. After tracheal intubation via video stylet, the ventilator was set with a tidal volume of 8 mLkg^-1^of ideal body weight and FiO_2_ 40 %. The respiratory rate and I: E ratio were adjusted to maintain inspiratory peak pressure of less than 30 cmH_2_O and normocapnia. During the whole surgery, propofol and remifentanil effect site concentrations will be adjusted to achieve BIS values of 40 to 50 and to maintain mean blood pressure and heart rate within 20 % of pre-induction values.

- **Postoperative management protocol**

Postoperative analgesia is standardized for all patients. If patients presented with breakthrough pain (NRS ≥ 4/10), IV ibuprofen 400 mg will be administered. If this proved ineffective after 30 minutes IV pethidine 50 mg will be administered. Postoperative nausea and vomiting are treated with intravenous metoclopramide 10 mg and ramosetron 0.3 mg. All patients resume diet and ambulation as soon as possible after full recovery from anesthesia unless gastrointestinal symptoms are noted. Hospital discharge is determined by the surgery team.

2) Randomization and blinding

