**12. Suspension/Dropout Criteria**

1) In case of a hemodynamically unstable state before and after anesthesia

2) When a previously undiagnosed patient has an allergic reaction to an anesthetic agent

3) Subject's voluntary withdrawal of consent

4) Failure to follow the instructions of the research doctor

5) Occurrence of a serious disease unrelated to study participation

6) In the case that Your doctor has decided that research is not the best option for participants.

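### The protocol calls the trial investigator blinded but lets the primary investigators know the pre-generated allocation list, so the label does not fit and upcoming allocations are not concealed from them

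*Protocol*

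**What the plan says.** Section 4, 3) states the design without qualification: "design: Single-center, randomized controlled study, investigator blinded".

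Section 9, 2) Randomization and blinding describes the arrangement:

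- Generation: "The randomization list was generated by a random permuted block design with a block size of two".
- Concealment: "The allocation information is sealed in an opaque envelope and piled up in a cabinet".
- Opening: "Gynecologist open the sealed envelope, in turn, to confirm the assignment information and distributed or not distributed chewing gum, accordingly".
- Access to the list: "Randomization information is managed so that the list is not disclosed to the evaluator and only primary investigators can know".

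Outcome recording has its own rules. In section 9, 2): "Anxiety levels prior to surgery and uncomfortable symptoms related to fasting will be recorded by an anesthesiologist who is not participating in the study", on the basis of patient self-report. In the standardized anesthesia protocol of section 9: "Another investigator who is not aware of group allocation will perform intubations and evaluate the degree of oral secretion during intubation". The postoperative questionnaires are guided by ward staff described as independent.

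Section 12 lists reasons for ending participation that call for judgment, among them "Failure to follow the instructions of the research doctor" and a decision by the doctor that the research is not the best option for the participant. Section 13 names the APAIS score and anxiety-related symptoms as the primary outcome.

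**The concern.** Read plainly, section 4 says that investigators do not know the allocation, and section 9 says that the primary investigators may. A report that repeats the section 4 label would claim a property that section 9 does not provide.

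The larger issue is concealment. Random allocation protects against selective enrolment only while the people who decide on eligibility, consent and order of entry cannot foresee the next assignment. A list made in advance and open to the primary investigators removes that protection for them, whatever is done with the envelopes. The same knowledge could enter the judgments in section 12 on who stays in the study, because nothing requires those to be made without knowledge of the arm. Both routes matter more here because the primary outcome is self-reported anxiety, which is likely to depend on how anxious a patient was before entry.

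**Working it through.** The plan gives no figure on this point, so the check is a comparison of the texts and a count of foreseeable allocations.

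**Who may know what, as written**

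| Role | Upcoming allocations | Allocation of a patient already assigned |
|---|---|---|
| Primary investigators | May be known (section 9 access sentence) | May be known |
| Gynecologist opening envelopes | Concealed by the envelope, except as counted below | Known |
| Patient | Not addressed | Known, since gum is given or not |
| Recorder of anxiety and symptoms | List withheld | List withheld |
| Intubating rater of oral secretion | List withheld | Stated to be unaware |

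Only the last two rows are blinded. That is blinding of evaluators. The access sentence has no end date, names no independent custodian and is not limited to patients already allocated. Section 6 has consent obtained one day ahead and section 9 has assignment on the evening before surgery, so enrolment and allocation lie close together. The protocol does not say who screens, consents or schedules patients.

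**How many allocations can be foreseen**

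Inputs: 104 patients, 52 per group (section 7), and a fixed block size of two (section 9). I assume one unstratified list, since no strata are mentioned.

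- With the list: 104 of 104.
- Without the list, but knowing the block size and all past assignments: 104 / 2 = 52 blocks. The first allocation in each block is a coin toss and the second is fixed by the first. Certain: 52 / 104 = 50%. Expected correct guesses: 52 × 1 + 52 × 0.5 = 78, and 78 / 104 = 75%.
- For comparison, fixed blocks of four with the size known: the distinct patterns, up to swapping the arms, are AABB, ABAB and ABBA, with 2, 1 and 1 allocations certain at the end of the block. The mean is 4/3 per block, so 26 × 4/3 = 34.7 of 104, or 33%. A larger block helps, but a known fixed size still leaks, so sizes should vary and be withheld.

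The block size is printed in the protocol, and whoever opens envelopes in turn sees past assignments. If several gynecologists share this task, each sees only part of the sequence and can foresee fewer.

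**The case against.** The strongest reply is that the conflict is one of terms. Section 9 itself calls the person who rates oral secretion an investigator, so the design line may mean only that evaluating investigators are blinded. The two sections would then agree, and the access sentence would simply describe restricted custody. This reading is possible, and it softens the contradiction. It does not rescue the label, which carries no qualifier and would be read more widely, and it leaves the concealment point untouched.

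A second reply is that bias is not shown. The protocol does not say that the primary investigators enrol patients, nor that the research doctor in section 12 is one of them. Envelopes are opaque, sealed and opened in sequence, and steering would need someone who both knows the list and controls entry. This stands: the documents show that access is permitted, not that it is used.

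A reader might infer that an unblinded investigator records the primary outcome. The documents do not support that, because an anesthesiologist outside the study records anxiety and fasting symptoms and the list is kept from evaluators. A reader might also infer that the false-positive rate is raised by some stated amount. Any such figure would need an assumed rate and strength of steering, and the protocol supplies neither. Nor can one say that an imbalance in prior anxiety would go undetected. The visible text describes one anxiety assessment, in the holding area, but the content under the Timeline heading in section 10 is not in the text available to me and may include an earlier measurement.

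**Conclusion.** The point holds in this form. The unqualified label in section 4 does not match the blinding described in section 9, and upcoming allocations are not concealed from anyone permitted to see the list. Its size is 104 of 104 allocations for a person with the list, and 52 of 104 certain (75% guessed correctly on average) for a person who knows only the block size and the complete past sequence.

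The conclusion about the label rests on the wording alone. The count without the list assumes a single unstratified sequence. The step from lost concealment to biased enrolment or withdrawal depends on who enrols and who decides on dropout, which the protocol leaves open. It is therefore a risk that should be removed, not a demonstrated bias.

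**What to change.** **Section 9, list custody.** Replace the access sentence with text to this effect: the list is generated and held by a person with no role in enrolment, outcome assessment or dropout decisions, and neither primary investigators nor evaluators have access until the database is locked. An existing uninvolved staff member, such as a department statistician or pharmacist, can do this.

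**Section 9, blocks.** Replace the fixed block size of two with larger, varying sizes that are not disclosed to enrolling staff. Moving the list alone would leave half the sequence foreseeable.

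**Section 4, label.** Replace the design line with a statement of roles. Blinded: the recorder of anxiety and symptoms, and the intubating rater. Not blinded: the patient, and the gynecologist who distributes the gum. Add that the primary outcome is self-reported by unblinded patients. A bare assessor-blinded label would also be inexact, because the symptom survey in section 10 asks whether chewing gum helped, and the answer may reveal the arm to the recorder.

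**Cost.** A wording amendment, a new list and a change of custodian. Group sizes may differ slightly if recruitment ends inside a block. With blocks of four and six, for example, a total of 104 could end at worst 53 to 51. The variance of the difference between means then changes by the factor (1/53 + 1/51) / (2/52) = 5408 / 5406 = 1.0004, which is negligible. If enrolment has already begun, apply the change to the remaining allocations and report the earlier arrangement as it was.

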**10. Outcomes and assessment**

1) Patient characteristics: Age, sex, height, weight, BMI, ASA class, and other comorbidities,

smoking, alcohol

2) Gastric fluid volume & pH

After taking the right lateral decubitus position, the diameter of the antrum is measured by abdominal ultrasonography.

The gastric fluid volume is calculated using the following formula.

* volume (ml) = 27 + 14.6 9 * antral area (cm²) – 1.289 * age (year)

After anesthesia induction is completed, gastric fluid is collected through an esophageal probe ad acidity is measured using a pH meter.

3) Pre-operative anxiety

(1) Anxiety with VAS

(2) Anxiety with APAIS score

[figure not shown]

The APAIS score was developed to measure patients' anxiety before surgery, and its effectiveness has been verified in several studies. The APAIS score is calculated by summing the scores from 1 to 5 for 6 questions. a

(3) Symptoms related to anxiety

Whether chewing gum during fasting helped to endure the fasting time, difficulty concentrating, and anxiety-related symptoms such as hunger, thirst, dry mouth, fatigue, headache, nausea, etc. were surveyed with a score between 0 and 10 for each item. do. (Questionnaire Attachment 1)

4) Recovery or bowel function

Post-operative nausea & vomiting

Flatus expulsion, defecation time in postoperative time, time of resume feeding

Intra-hospital bowel complication (ileus, dyspepsia, abdominal pain)

5) QoR15

QoR 15 is calculated by the total sum of the patient's postoperative recovery by asking questions on a scale from 0 to 10 for each item. The higher the score, the higher the quality of recovery.

6) Other Observation Items

(1) The amount of oral secretion at the time of intubation (none/ mild/ moderate/ severe)

(2) Total dose of the anesthetic drug used during anesthesia, amount of fluid

(3) Total anesthesia time and operation time

(4) Total amount of opioids used in the intrahospital period

7) Timeline

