**9. Methodology**

1) Time flow

1. The patient is assigned to either the experimental group or control group on a random basis on the eve of the operation. All patients scheduled for gynecologic surgery were instructed to fast overnight before surgery, and oral carbohydrate drink (NO NPO^Ⓡ^: Daesang, Seoul, South Korea) loading was used routinely according to the protocol of the department of gynecology
2. The patients in the control group (CHD group) are requested to follow the aforementioned fasting guideline. The participants were instructed to consume at least 600 mL to 800 mL of carbohydrate drinks up to 3 hours before induction of anesthesia.
3. The patients in the test group (CHD with gum group) follows the fasting protocols of our gynecologic strategy and were encouraged to chew gum freely with oral carbohydrate loading during fasting time.
4. There is no intervention other than chewing gum during fast times between the two groups of patients.
5. Gum will be removed right before being transported to the operating room before transfer. The nurse in charge of the operating room double-checks whether or not gum has been removed during the patient identification process in the preoperative holding area.
6. The severity of anxiety would be examined at the preoperative holding area immediately before surgery.
7. In the operating theater, all participants are provided with supplemental oxygen. During pre-oxygenation, a gastric ultrasound exam is performed by [name].
8. The independent anesthesiologist will induce general anesthesia according to the standardized protocol. Propofol and remifentanil are used using a TCI machine with the aim of a Bispectral Index of 40-60. Blood pressure and heart rate were maintained within 10% of baseline. The blinded anesthesiologist will rate the oral secretion during tracheal intubation.
9. Gastric juice is naturally drained via an esophageal temperature probe (ST probe) during surgery and analyzed with an acidity analyzer.
10. In the course of surgery and maintenance of anesthesia, the subsequent process proceeds without special intervention. Total anesthesia time, operation time, drugs used during anesthesia, and vital signs are collected through medical records. (Attachment of case reporting form)
11. Afterward, the treatment and recovery of patients in the ward will be proceeded according to the general guidelines of the department of obstetrics and gynecology based on the ERAS protocol.

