**13. Outcomes and statistical analysis**

1) Primary outcome: Anxiety with APAIS score, Symptom related to anxiety

2) Secondary outcome: Flatus expulsion or defecation time in postoperative time, time of resume feeding, Intra hospital bowel complication, gastric fluid volume & pH, oral secretion at intubation time, QoR 15 score

3) Analysis

All continuous data are compared with Student’s t-test or Wilcoxon’s rank sum test according to normality. All categorical variables are analyzed using the chi-square test, Fisher’s exact test. The descriptive variables will be presented as mean ± standard deviation or median with an interquartile range. The categorical data are summarized as the number (%). The difference in APAIS, the primary outcome will be compared using student’s t-test. The multiple comparisons for sub-scores of APAIS would be adjusted with Bonferroni correction.

The association between QoR-15K and APAIS scores measured in the preoperative holding area will be analyzed using linear regression model.

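### The primary symptom set includes an item on whether gum helped, which controls cannot answer and which can disclose the arm to the person recording it

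*Protocol*

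**What the plan says.** - **Primary outcome.** Protocol Section 13, item 1: "Primary outcome: Anxiety with APAIS score, Symptom related to anxiety". The analysis text in the same section then calls APAIS alone the primary outcome. It also sends all continuous data to a between-group test and makes no exception for any symptom item.
- **Content of the symptom set.** Section 10, item 3)(3), under the heading on anxiety-related symptoms, opens its list with "Whether chewing gum during fasting helped to endure the fasting time". It goes on to hunger, thirst, headache and similar complaints, all of which "were surveyed with a score between 0 and 10 for each item". The full form is Questionnaire Attachment 1, which is not among the documents.
- **Who receives gum.** Section 9, item 2): the gynecologist opens the envelope and "distributed or not distributed chewing gum, accordingly". The same paragraph adds: "There is no intervention other than chewing gum during fast times between the two groups of patients".
- **Who records.** Section 9, item 2): "Anxiety levels prior to surgery and uncomfortable symptoms related to fasting will be recorded by an anesthesiologist who is not participating in the study", on the basis of patient self-report.
- **Blinding.** Section 4, item 3) describes an investigator-blinded design. Section 9, item 2) adds: "Randomization information is managed so that the list is not disclosed to the evaluator". Randomization is in permuted blocks of two.

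**The concern.** An outcome can be compared between arms only if the question means the same thing in both. A question on whether gum helped does not, because only one arm was given gum. As written, it nevertheless sits under a heading that Section 13 names as primary, so the planned comparison of continuous data would take it in. A difference on this item could then be reported as a primary finding although it says nothing about how hungry, thirsty or uncomfortable patients were.

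The second issue is blinding. The protocol protects its anxiety outcomes by keeping allocation from the evaluator. A question about gum, put by the person who also records anxiety, can give that allocation away in the answer.

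**Working it through.** **Inputs.** 104 patients, 52 per arm (Section 7); block size two (Section 9); items scored 0 to 10 (Section 10); gum in one arm only (Section 9); anxiety VAS 39.31 with SD 17.04, 25% difference, 5% alpha, 80% power (Section 7).

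**Step 1. The plan's own figure, as background.** The difference is 0.25 × 39.31 = 9.83. With n = 2(z₀.₉₇₅ + z₀.₈₀)² × SD² / difference², this gives 2 × (1.960 + 0.842)² × 17.04² / 9.83² ≈ 47.2, which rounds up to 48 per arm against 47 stated. Power at 47 per arm is 0.798, so the figure reproduces within rounding. For dropout, 47 × 1.1 = 51.7, or 52 as stated; 47 / 0.9 = 52.2 would give 53. The calculation rests on the anxiety VAS alone, so nothing done to the gum item changes it.

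**Step 2. What a control can answer.** Let m be the gum-arm mean on the item and c the value entered for controls. The between-arm difference is m − c.
- If controls leave it blank or mark it not applicable, there are no control data and no comparison.
- If controls are scored 0, the difference is m − 0 = m. The documents give no value for m, so it may lie anywhere from 0 to 10. Taking m = 5 purely as an assumption, the difference is 5 points.

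In neither case does the result depend on whether gum changed fasting discomfort. It depends on who was given gum. This affects one item for all 52 controls.

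**Step 3. What the answer discloses.** Section 9 gives anxiety and fasting symptoms to one recorder. If that recorder also takes the gum item, a substantive answer points to the gum arm and a blank or not-applicable answer points to control. The order of the forms is not fixed. If the gum item came before APAIS and VAS, the recorder could know the arm before recording anxiety in up to 104 of 104 patients.

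**Step 4. Why order alone does not close the leak.** Suppose VAS and APAIS always come first. Within one patient the disclosure then comes too late to matter. But 104 / 2 = 52 blocks, each holding one patient per arm, so learning the arm of the first patient in a block fixes the arm of the second. Up to 52 of 104 patients could still be predicted before their anxiety is recorded. This is an upper bound: it requires the same recorder to see both patients, to know or guess the block length, and to know which patients are paired.

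**The case against.** The strongest reply is that the form itself is not available. Section 10 is a one-sentence summary that points to Attachment 1, which may hold a control version, a not-applicable box or a fixed order. The sentence can also be read as setting the gum question beside the symptoms and not among them, and Section 9 does not say in terms that the anesthesiologist takes it. This limits how certain the leak is. It does not remove the problem in the protocol text, which places the item under a heading named as primary and gives no rule for controls. Item content and the choice of recorder are protocol matters; an analysis plan could leave the item out of the comparison, but it could neither supply a valid control answer nor restore blinding.

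A second reply is that anxiety is self-reported by patients who know whether they chewed gum, so the recorder's knowledge adds little. This stands in part: recorder unblinding adds to a bias already present. It is still the safeguard the protocol chose.

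Four stronger readings are tempting, and the documents do not support them.
- *A reader might infer that a symptom total is distorted by up to 10 points, or by reverse scoring of this item.* No total is defined; scores are per item, the list is open-ended, and the anchors are not shown.
- *A reader might infer that the whole primary outcome is invalid.* APAIS does not contain this item, and Section 13's analysis text treats APAIS as the primary outcome.
- *A reader might infer that evaluator blinding is lost altogether.* That depends on who takes the item and when, and neither is settled by the text.
- *A reader might infer that the gum check also unblinds the recorder.* Section 9, item 1) has the operating-room nurse, who "double-checks whether or not gum has been removed during the patient identification process in the preoperative holding area". Nothing says that the anxiety recorder is present.

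**Conclusion.** The concern holds for one item and for one route of disclosure. As written, the gum item has no valid control answer, so a between-arm comparison of it is uninterpretable: either no control data, or a difference equal to the gum-arm mean. If the anxiety recorder takes the item, evaluator blinding is weakened for up to all 104 patients when it is asked first, and for up to 52 when VAS and APAIS come first. These counts are ceilings. They assume full enrolment, the same recorder within a block and, for the figure of 52, awareness of the block length. The size of any resulting bias in APAIS or VAS cannot be worked out from the documents.

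APAIS, VAS and the remaining symptom items can still be compared between arms, and the sample size is unaffected. The change should be made before data collection, because neither a neutral answer nor recorder blinding can be recovered afterwards.

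**What to change.** 1. Replace the gum item in Section 10, item 3)(3) and in Attachment 1 with one arm-neutral question put to every patient: *How hard was it to endure the fasting time?*, 0-10, high = worse.
2. If gum acceptability is wanted, collect it in the gum arm only, after surgery, as a descriptive item outside the primary outcome and not through the anxiety recorder. Section 9 already has ward staff guiding the postoperative questionnaires.
3. State that VAS and APAIS are completed before the symptom items. This is a useful addition but not a substitute for step 1, because of the blocks of two.
4. Leave the gum-removal safety check as it is.

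The cost is one reworded questionnaire line, one separate descriptive item and one sentence on order. Sample size and staffing do not change.
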